## Background

While recent reports indicate a plateau in the rate of childhood obesity in the United States, the number of obese children remains high [1]. In 2011–2012, obesity affected 17 % of US youth, with 31.8 % being classified as overweight or obese [1]. Significant differences in prevalence of obesity exist between racial, ethnic and age groups. Non-Hispanic black and Hispanic youth are significantly more affected by obesity than their non-Hispanic White and non-Hispanic Asian peers [1]. Additionally, there appears to be a developmental trajectory in prevalence of obesity as 8 % of 2- to 5-year olds, 17.7 % of 6- to 11-year olds, and 20.5 % of 12- to 19-year olds were classified as obese in 2011–2012 [1]. So while it appears that the rise in obesity has tapered off, the prevalence of overweight and obesity among US youth remains concerning due to its devastating consequences, which affect the physical and mental health of children, as well as their academic success [2, 3].

Emerging research has begun to point to particular windows of risk for child weight gain. Troubling data indicate that school-age children experience unhealthy gains in BMI at a rate nearly twice as fast during the summer months when school is out of session compared to the school year [4–10]. African American and Hispanic, minority groups and economically disadvantaged children, subpopulations already at increased risk for obesity, as well as girls, may be particularly vulnerable to unhealthy weight gain during these non-academic months [1]. Limited knowledge of the external factors that lead to altered diet and physical activity during the summer time is available to adequately explain the unfavorable weight gain occurring in many children during this window of risk [11].

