Camp Nutrition Education Recreation and Fitness (NERF) is a multi-component, evidence-based nutrition, physical activity, and mental health intervention that is coupled with USDA SFSP open sites in Columbus, Ohio. To our knowledge, this is the first multi-component, evidence-based intervention to address the disproportionate childhood weight gain in underserved children during the summer months. The long-term goal is to develop and implement effective theory-based community nutrition and physical activity interventions for childhood obesity prevention, particularly in underserved minority children, aimed at empowering children to make healthy dietary and physical activity choices and achieve a healthy weight and, ultimately, overall optimal health and wellness. The primary aims of this research project are to:Evaluate the efficacy of Camp NERF to improve child nutrition, physical activity, mental health, and anthropometric outcomes.Hypothesis 1.1: Diet quality, physical activity and sedentary time, positive and negative affect, BMI z-scores, and waist circumference (WC) z-scores will improve more from baseline to post-intervention among children participating at the Enhanced Care sites compared to Standard Care and Active Control sites.
Evaluate the efficacy of Camp NERF to improve caregiver self-efficacy for establishing healthy family nutrition and physical activity practices, amount of physical activity, and BMI.Hypothesis 2.1: Caregiver self-efficacy scores for establishing healthy family nutrition and physical activity practices, physical activity score, and BMI will improve more from baseline to post-intervention among families participating at the Enhanced Care sites compared to the Standard Care and Active Control sites.
Evaluate the efficacy of Camp NERF to improve youth mentor nutrition, physical activity, and anthropometric outcomes.Hypothesis 3.1: Diet quality, physical activity and sedentary time, positive and negative affect, BMI z-scores, and waist circumference (WC) z-scores will improve among youth mentors from baseline to post-intervention.

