### Participants and recruitment

The target population for Camp NERF is underserved minority children entering kindergarten through fifth grade and their adult caregiver from urban neighborhoods in Columbus, Ohio. Participants will be recruited through a variety of methods including, but not limited to, school announcements, emails, flyers, phone calls, and neighborhood canvassing. Prior to enrollment in the study, a consent form, parental permission form, and assent form will be completed by the caregiver and child, respectively.

Also, data will be collected from high school students who will serve as Youth Mentors for the child participants at the Camp NERF Enhanced Care sites. The Youth Mentors will be recruited through a collaborating partner, the Godman Guild Association that provides internships to high-school aged students during the summer months through Temporary Assistance for Needy Families (TANF) funding. Prior to study enrollment, a parental permission form and assent form will be completed by the caregiver and Youth Mentor, respectively, for those under the age of 18. Youth Mentors 18 years of age or older will complete consent forms prior to enrollment in the study. Individuals who are not interested in enrolling in the study will still be able to participate as Camp NERF Youth Mentors.

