#### Data analysis

The intervention will be tested by comparing change from baseline to post-intervention in diet quality, physical activity, mental health, and anthropometric outcomes for child participants (hypothesis 1.1) and psychosocial, physical activity, and anthropometric outcomes for adults (hypothesis 2.1). For each outcome variable of interest (Table 2), a mixed effects linear regression model will be fitted with site-type as the primary predictor. Other covariates will include race/ethnicity, income, and attendance, as well as baseline zBMI for all models that do not include weight status as the primary outcome. Using a mixed effects linear regression model allows us to capture the contributions of two sources of variability: (1) a between-site variability and (2) a between-subject or within-site variability. Impact of Camp NERF on Youth Mentors will be tested by comparing change from baseline to post-intervention in diet quality, physical activity, mental health, and anthropometric outcomes (hypothesis 3.1) using multiple linear regression analyses.

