#### Youth mentor-assisted education

The use of peer-led interventions have been utilized among youth in areas pertaining to the use of alcohol, tobacco, illegal drugs, violence, and sexual behavior [43–50]. Data indicate that mentored youth compared to un-mentored youth are less likely to participate in these aforementioned risky behaviors [51, 52] and are more likely to succeed academically [53–56]. Until recent years, use of peers as an intervention strategy to improve nutrition and physical activity, and ultimately weight status, had not been employed, but emerging research has demonstrated positive results for biometric-, nutrition-, and physical activity-related outcomes [43, 56–68]. According to the SCT, self-efficacy is influenced by role modeling the behavior [69]. As such, the peers leading the education may experience positive behavior change as a result of child mentoring. Unfortunately, the educating of peer mentors has been understudied [56, 64, 65, 67, 68].

Youth Mentors from the neighborhoods in which Camp NERF will be implemented will be recruited and will assist in the Camp NERF education delivery at the Enhanced Care sites. The Youth Mentors will undergo a 20-h work-readiness training, as well as will attend the 2-hour weekly Camp NERF staff meetings, where feedback will be provided on the lessons for the current week and the upcoming weeks lessons will be reviewed and practiced. Additionally, professional development topics, such as how to interact with co-workers in the workplace, will be discussed in collaboration with the undergraduate- and graduate-level Camp NERF Counselors.

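### Aim 3 claims efficacy and impact of Camp NERF for Youth Mentors, but mentors serve only at Enhanced Care sites and are compared only with their own baseline

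*Protocol article*

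**What the plan says.** All references are to the protocol article.

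- **Aim (Background).** Among the primary aims is: "Evaluate the efficacy of Camp NERF to improve youth mentor nutrition, physical activity, and anthropometric outcomes". Hypothesis 3.1 states that the outcomes, including BMI and waist circumference z-scores, "will improve among youth mentors from baseline to post-intervention". It names no comparator. Hypothesis 1.1 does name one: "among children participating at the Enhanced Care sites compared to Standard Care and Active Control sites". Hypothesis 2.1, for caregivers, names the same two.
- **Where mentors are (Participants and recruitment; Youth mentor-assisted education).** Data come from "high school students who will serve as Youth Mentors for the child participants at the Camp NERF Enhanced Care sites". Mentors "will assist in the Camp NERF education delivery at the Enhanced Care sites". Educator training and structure says the same. No youth in the other two arms, or outside the programme, are described.
- **Analysis (Data analysis).** Children and caregivers get a mixed model with site type as the main predictor. For mentors: "Impact of Camp NERF on Youth Mentors will be tested by comparing change from baseline to post-intervention", by multiple linear regression.
- **Goals (Table 2).** For mentors' weight, waist and blood pressure, the goal is to prevent an increase.
- **Limitations (Discussion).** The article concedes that there is no true negative control group and explains this by the right of children and families to attend the meal sites. It does not mention the mentors.

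**The concern.** Efficacy and impact are causal words. For children and caregivers the randomised arms support them. For mentors nothing does, because every mentor is in one arm and the only reference is the mentor's own baseline. If the plan is followed as written, a p-value for change over the summer will be reported as evidence on a primary aim. Nothing in the design would show whether Camp NERF produced that change. An analysis plan can refine the model, but it cannot supply a comparison group that was never recruited.

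**Working it through.** The article gives no sample size, SD, effect size or power for mentors, so there is no stated figure to reproduce. The check is of design logic, followed by an illustration.

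**1. What the pre-post comparison estimates.** Let *e* be the programme effect on a mentor outcome and *b* the change that would have occurred anyway. The expected mean change is m = e + b. For children, the difference between arms is (e + b) − b = e, because randomisation balances *b* in expectation. For mentors there is no second term to subtract, so *e* and *b* are not separately identified. The bias in reading m as e is exactly *b*.

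**2. What *b* can contain, from the article itself.**
- Season: the Background says "school-age children experience unhealthy gains in BMI at a rate nearly twice as fast during the summer months".
- Maturation over the summer.
- Repeat testing: the same assessment form is used at baseline and post-intervention (Impact measures).
- The internship, with 20 hours of work-readiness training and professional development topics in the weekly meetings (Participants and recruitment; Youth mentor-assisted education).

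The 4H Programming section justifies an active control for children on the ground that programme content must be told apart from exposure to structured activity as such. The same reasoning applies to mentors, who have no such control.

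**3. Goal against test.** Suppose summer would raise BMI z-score by b > 0 and the programme prevents all of it, so e = −b. Then m = 0. The prevention goal in Table 2 is fully met, yet hypothesis 3.1, which requires improvement from baseline, is not supported. If instead e = 0 and b < 0, then m < 0 and hypothesis 3.1 is supported with no programme effect. Prevention can be judged only against what would otherwise have happened.

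**4. Illustration.** All inputs are assumed: change score with SD 1, one mean-centred covariate, ordinary least squares, two-sided alpha 0.05, 2,000 runs per cell. The test is of the adjusted mean change (the intercept), with noncentrality (e + b)√n and n − 2 degrees of freedom. Only the sum e + b enters, so the two scenarios have the same rejection probability; differences below are simulation noise.

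| Mentors (assumed) | Noncentrality 0.5√n | Rejected: e = 0.5, b = 0 | Rejected: e = 0, b = 0.5 |
|---|---|---|---|
| 12 | 1.73 | 33% | 35% |
| 20 | 2.24 | 56% | 58% |
| 40 | 3.16 | 88% | 88% |

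**5. Site, a secondary matter.** Twelve sites in three groups give 12 / 3 = 4 Enhanced Care sites if allocation is equal, which the article does not state. With 4 sites, an assumed intraclass correlation of 0.05 and no true change, ordinary regression rejected in 5.9%, 7.4% and 10.2% of runs for 12, 20 and 40 mentors, against a nominal 5%.

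**The case against.** Several points can fairly be made in defence of the plan.

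- *Hypothesis 3.1 claims only within-group improvement, and a regression of change scores can test that.* This stands. A reader might infer that the named regression cannot test the hypothesis, or that uncentred covariates would make its intercept meaningless. The documents support neither. The adjusted mean change tests hypothesis 3.1, as the table shows. The article names no mentor covariates, no coding and no tested coefficient, and an article may leave these to a fuller document. The mismatch is between the words efficacy and impact and the design.
- *The documented summer drift points against a false claim.* For BMI this is right: if summer raises BMI, the uncontrolled comparison is biased against showing improvement. The Background figure is also for school-age children in general, with no figure for high-school mentors, and z-scores remove much of average growth. So the direction of bias is unknown, and for diet, activity and affect the article cites no drift at all. That the effect is unidentified does not depend on direction.
- *Mentoring is itself the exposure.* Partly so: the article expects mentors to change through mentoring. If the whole internship package is taken as the exposure, the internship stops being a rival explanation. Season, maturation and repeat testing remain.
- *Mentors are outside the randomised comparison.* True, and it limits the reach of the point. It does not license causal wording for them.

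**Conclusion.** The point holds. Aim 3 and the mentor sentence in Data analysis claim a causal result that a single-group pre-post comparison cannot give, and the stated limitations do not cover it. The size of the bias is the entire background change over the summer. It cannot be quantified from the article and could run in either direction. The simulated rejection rates rest on assumed mentor numbers and an assumed 0.5 SD drift. They show that effect and drift are indistinguishable; they are not a forecast for this trial. The site-clustering figures rest further on an assumed equal split of sites and an assumed intraclass correlation.

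A reader might go further and conclude that the trial's main results are compromised. They are not, because the child and caregiver hypotheses have randomised comparators and do not use mentor outcomes. This is a correction to what may be concluded on one of the primary aims, and it should be made.

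**What to change.** 1. Reword Aim 3 and the mentor sentence in Data analysis as an exploratory description of within-mentor change, without efficacy or impact. Hypothesis 3.1 is already a within-group statement and needs only the exploratory label.
2. Report the mean change for each mentor outcome (adjusted mean change if covariates are used) with a 95% CI that allows for site where feasible. With about 4 sites, such an interval will be imprecise, and this should be said.
3. State that no efficacy conclusion will be drawn for mentors, including for the prevention goals in Table 2.
4. Add the missing mentor comparator to the limitations in the Discussion.

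The cost is wording, and the loss of an efficacy claim that the design cannot support. If the sponsor wants to keep that claim, it would need a comparison group of similar youth measured at the same two times, which means added recruitment and data collection.

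### The Youth Mentor analysis (hypothesis 3.1) makes no stated allowance for site, so its standard errors are too small if mentors at the same site change alike (minor)

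*Protocol article*

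**What the plan says.** The Background section of the protocol article introduces its list with "The primary aims of this research project are to". The third item is "Evaluate the efficacy of Camp NERF to improve youth mentor nutrition, physical activity, and anthropometric outcomes". Hypothesis 3.1 under it is a one-group statement that outcomes "will improve among youth mentors from baseline to post-intervention".

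The Data analysis section specifies a mixed effects linear regression for children and caregivers and gives the reason: "Using a mixed effects linear regression model allows us to capture the contributions of two sources of variability: (1) a between-site variability", alongside variability between subjects within a site. The paragraph ends with the mentors, whose change from baseline is tested for diet, activity, mental health and "anthropometric outcomes (hypothesis 3.1) using multiple linear regression analyses". It names no site term, random effect or covariates for that model, and gives no reason for the change of method.

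The section on youth mentor-assisted education says that mentors come from the neighborhoods where the program runs and that they "will be recruited and will assist in the Camp NERF education delivery at the Enhanced Care sites". The section on educator training and structure assigns three counselors to each site and has the mentors assist the counselors at Enhanced Care sites.

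**The concern.** Ordinary regression treats each mentor's change as an independent observation. Mentors at one site work with that site's counselors and children, in that site's food and activity environment. The article itself treats site features as possible influences: the process evaluation section plans post-hoc analyses of whether they contributed to outcomes. A shared site component in mentors' diet, activity or affect is therefore plausible.

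If it exists, the mean change varies more than the regression allows. Intervals are then too narrow and improvement is declared more often than the nominal rate, for every mentor outcome. This is separate from the lack of a comparison group, because even a purely descriptive pre-post interval would be affected.

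**Working it through.** **The plan's own figure.** There is none for mentors: no sample size, power, alpha or ICC. The article's only power figure, approximately 70%, concerns change in child BMI z-score and does not bear on this point.

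**Inputs**
- Sites: 12 randomized to 3 groups (Research design). Equal allocation is assumed, which gives 12/3 = 4 Enhanced Care sites.
- Mentors per site, m: not given. Values from 1 to 10 were tried.
- ICC of mentor change scores: not given. Values from 0 to 0.10 are shown.
- Each mentor is assumed to stay at one site.
- Test: mean change of zero, two-sided 5%, no covariates. This is the intercept test of a regression with independent errors.

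**Step 1: standard error.** The variance of the mean change is multiplied by the design effect DE = 1 + (m − 1) × ICC. The ratio of the ordinary to the correct standard error is about 1/√DE. At ICC 0.05:
- m = 3: DE = 1 + 2 × 0.05 = 1.10, ratio 0.95
- m = 5: DE = 1 + 4 × 0.05 = 1.20, ratio 0.91
- m = 10: DE = 1 + 9 × 0.05 = 1.45, ratio 0.83

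**Step 2: false-positive rate with site ignored.** Each cell is from 200,000 simulated datasets with 4 sites, a site effect of variance ICC and a residual of variance 1 − ICC. The t-test on all mentors has 4m − 1 degrees of freedom.

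| Mentors per site | ICC 0 | ICC 0.01 | ICC 0.05 | ICC 0.10 |
|---|---|---|---|---|
| 1 | 5.0% | 5.0% | 5.0% | 5.0% |
| 3 | 5.0% | 5.2% | 6.1% | 7.2% |
| 5 | 5.0% | 5.4% | 7.3% | 9.7% |
| 10 | 5.0% | 6.0% | 10.3% | 15.5% |

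A t-test on the 4 site mean changes (3 degrees of freedom) stays at 5% throughout.

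**Step 3: would an unstated fixed site term help?** Not for a conclusion beyond these particular sites. It removes site variation from the error term but not from the variance of the mean change. At ICC 0.05 the rate for the average change is about 7.8% with 5 mentors per site and 10.9% with 10, slightly worse than ignoring site.

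**Step 4: what the power difference shows.** For an assumed true change of 0.5 SD with 5 mentors per site, power is 56% for ordinary regression and 30% for the site-mean test at ICC 0.05. At ICC 0, where ordinary regression is exactly valid, it is 56% against 34%. The gap is therefore already 56 − 34 = 22 points with no clustering at all. Most of it comes from having 3 degrees of freedom.

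**The case against.** The strongest objection is that the error is conditional and may be small. A reader might infer that the mentor standard errors are definitely too small and that improvement will be declared too often. The article does not support that. It does not say how many mentors there are, how they are spread over sites, whether each stays at one site, or how strongly their changes correlate. Its only statement on site variance, in the power paragraph, takes it to be negligible. Part of the mentors' exposure is not described as site-specific: "The Youth Mentors will undergo a 20-h work-readiness training, as well as will attend the 2-hour weekly Camp NERF staff meetings". With 2 or 3 mentors per site and ICC up to 0.05, the excess is about 1 percentage point or less. All of this stands, and the point is worded accordingly. The negligible-variance assumption, however, was made for child BMI z-score, and the article still models site for children.

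A reader might also take the lower power of a site-level test as evidence of the error. It is not: the gap is mainly a cost of the remedy.

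A further objection is that a condensed article may leave model terms to a fuller document. That holds for covariates and mentor numbers. It does not cover a method that is named here and that differs, without explanation, from the one named earlier in the same paragraph.

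Finally, 4 sites give a poor estimate of a site variance. With 5 mentors per site the balanced-design estimate is zero or negative in about 48% of datasets at ICC 0.05 and 56% at ICC 0.01. This stands and shapes the fix. It is also fair that the missing comparator limits any claim of impact on mentors far more than clustering does.

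**Conclusion.** The point holds conditionally and is minor. The stated mentor model omits a site component that the same paragraph includes for the other participants, for an aim listed as primary. With more than one mentor per site and a positive within-site correlation, its standard errors are too small and its false-positive rate exceeds 5%. At ICC 0.05 the rate is about 6% with 3 mentors per site, 7% with 5 and 10% with 10. At ICC 0, or with one mentor per site, there is no inflation. These figures rest on 4 Enhanced Care sites, equal numbers of mentors per site, each mentor at a single site, and ICC values that the article does not give.

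**What to change.** In the Data analysis section, replace multiple linear regression for hypothesis 3.1 with the linear mixed model already used for children and caregivers: a random site effect with small-sample degrees of freedom. Add a t-test on the site mean changes as a sensitivity analysis. The two are not interchangeable, because the site variance will often be estimated as zero and the t-test leaves little room for covariates. State the number of mentors per site, and report the mentor mean change and its interval as exploratory.

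The cost is about one sentence of analysis wording and no new data. Intervals will be wider and power lower, because only about 4 sites carry mentors.
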